### Additional assessments

With additional funding, the core study is being extended with additional assessments taking place during the annual health assessment. Informed consent is obtained through the same school bag approach used in the core study.

*Physical activity* (study years 1, 2, 3 and 4): Each child is fitted with an Actigraph accelerometer and provided with instructions (verbal and paper) on its use. Children are requested to wear the monitor during waking hours for 7 days after which they are collected from the school. Children answer a question on their route to school and means of transport on the day of assessment. Children in some schools have the option of wearing a GPS (Global Positioning Satellite) monitor for a week to track the routes they take to and from school.

*Capillary blood test for SARS-CoV-2 antibodies and heavy metals* (study year 4 and 5): Children with informed consent provide a finger-prick capillary blood sample for testing on a Fortress COVID-19 rapid antibody lateral flow test cassette, the coating antigen for which is recombinant Spike-RBD-Human Fc fragment [34]. Children are given a letter to take home giving their antibody test result, its interpretation, and advice to follow current UK Government COVID-19 guidance.

### NHS health records

Following approval by an NHS research ethics committee and with participants’ informed consent we are approaching the Caldicott Guardians of participants’ general practices or the relevant local primary care health care record data service to request electronic downloads of coded electronic health record data from birth to current age, addressing respiratory, mental health, COVID-19 testing and vaccination status, and health care use. Data collection takes place during year 4 and 5 of the study.

### Air pollution modelling

Monthly exposure estimates will be produced at 20m^2^ resolution over the study domains using the CMAQ (The Community Multiscale Air Quality Modelling System)-urban model which couples the Advanced Dispersion roads Model (ADMS) with the Weather Research and Forecasting model WRF meteorological model and CMAQ regional scale models. A comprehensive description of the CMAQ-urban model has been published previously [35–37] and will be employed in the present study to model NOx, NO_2_, O_3_, PM_2.5_, PM_10_, PM (Primary Organic Aerosol (POA), Secondary Organic Aerosol (SOA), nitrate, sulphate, black carbon), as well as exhaust and non-exhaust PM contributions over the period 2018–2020. Model outputs will be provided at residential address level.

### Data protection and management

Participants are allocated a unique study ID number. Data collection, confidentiality, entry, security and storage and protection is managed according to principles of good clinical practice and in line with our Clinical Trials Unit protocols.

Data handling and record keeping are overseen by the Pragmatic Clinical Trials Unit (PCTU) based at QMUL. The Data Manager has developed appropriate data management strategies for the study and advises on their implementation. Advice is provided on current regulatory framework regarding data protection and data management procedures in compliance with the Data Protection Act and trial regulations. All databases have integrated data validation checks and audit trails. The PCTU data management team advise on electronic data security. They will also advise on data transfer, storage, back-up and archiving of data and ensure databases are regularly backed up and data safeguarded from accidental loss. Paper records, CRFs and informed consent forms and recruitment logs are held locally in line with governance procedures.

### Data

#### Statistical methods

The primary outcome variable of post bronchodilator FEV_1_, and secondary outcome variables of air pollution, post bronchodilator FVC and physical activity will be analysed longitudinally through a mixed effect model. The model assesses the interaction effect of time and study group to determine the difference in variable change between the intervention group (London) and comparison group (Luton). Mixed effects models using a random intercept term are robust to the biases of missing data and the clustering effect of recruiting participants from multiple schools, facilitating a longitudinal design in a highly transient population. Primary and secondary outcome variables will be adjusted to account for known covariates of gender, asthma diagnosis, ethnicity, deprivation, [38] age, height, and BMI. Secondary covariates which may be included after sensitivity analysis include socioeconomic status, stress, and physical activity. For linking air pollution data with lung function over time, a more complex mixed effect model with three levels will be used, the levels being child, school, and group. These will be tested first on a complete model with all levels, if models are not identifiable, then simpler models will be tried with fewer levels. These models would allow for the effects of each air pollutant to be tested against lung function at each level as well as over time.

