There is therefore an urgent need to identify the most impactful policy interventions that improve air quality and deliver health benefits. Low Emission Zones (LEZ), which restrict the entry of polluting vehicles to urban areas, and related Clean Air Zones, have become the dominant public health policy intervention in the effort to improve air quality across Europe [15]. To date, studies evaluating their impact have shown variable effects on road use, [16] exhaust emissions, and air quality, with few identifying clear health benefits [5, 17–24]. A systematic review which evaluated the impact of air quality strategies across Europe on health and health inequalities found negligible effects on respiratory symptoms [23] with only one of 15 the studies identified gathered health data directly from individuals [24]. There was limited evidence for impact of LEZs on air quality in five EU countries (Denmark, the Netherlands, Germany, Italy and the UK) though the health impact of these changes were not addressed [25]. A recent Cochrane systematic review focusing on interventions to reduce ambient particulate matter air pollution and their effect on health identified few studies, with only low or very low grade evidence that interventions targeting vehicular sources improved air quality or health [26].

London implemented its first LEZ from 2008 to 2012, with phased tightening of emission standards in 2008 and 2012. We evaluated its impact, using a sequential cross sectional design, on the health of 2,297 east London primary school children, [5, 27] finding small improvements in air quality (most clearly NO_2_ reductions at the roadside), but no convincing health benefit, such as improvements in lung function or respiratory symptoms.[29] Furthermore, over the study period, we identified significant deficits in participating children’s lung capacity of between 5 and 10%, associated with exposures to traffic-related pollutants.

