### Sample size

We use 90% power and 0.05 significance level to test a 15 ml difference in FEV_1_ growth per year between Central ULEZ and Luton comparison cohorts. For 40 schools/arm with 40 children from any of school years 2, 3, or 4, the study is powered for 15ml per year difference in FEV_1_ growth between the comparison zone and ULEZ. The total target sample size is therefore 3,200 children, comprising 1,600 in the London cohort and 1,600 in the Luton cohort.

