### Assumptions

Adjustment for clustering of lung function outcomes within schools, by inflating sample size using an intra-class correlation (ICC) for FEV_1_ in schools calculated from our original ULEZ study (ICC = 0.001).70% success rate in children in classes Y2 and Y3 for a valid reading for FEV_1_.20% attrition per year of follow up, reflecting children moving schools or withdrawing.30% inflation to enable subgroup analysis.

With COVID-19 lockdowns closing schools and leading to loss of data collection during study years 2 and 3, we calculate that addition of a 5th year of data collection with follow up of children moving to secondary schools during study years 4 and 5 will deliver study power as follows:

25% capture of movers to secondary schools retains 80% power.50%, 75% and 100% capture of movers retains over 90% power.

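### The primary growth contrast in ml/year depends on scale: a proportional London–Luton gap in FEV1 level would show as a growth difference without any ULEZ effect, so a log-scale companion analysis should be pre-specified

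*Protocol article*

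**What the plan says.** Under Outcome measures, the primary outcome is lung growth, measured as post-bronchodilator FEV1. The Sample size section fixes the effect in absolute units. The study is designed "to test a 15 ml difference in FEV_1_ growth per year between Central ULEZ and Luton comparison cohorts", at 90% power and a significance level of 0.05.

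Statistical methods describes a longitudinal mixed model with a random intercept: "The model assesses the interaction effect of time and study group to determine the difference in variable change". Gender, asthma diagnosis, ethnicity, deprivation, age, height and BMI are named as adjustment covariates. No covariate-by-time term is named. No log, percent-predicted or reference z-score version of FEV1 appears. The z-scores under Sensitivity analyses and missing data are an outlier screen, and none of the sensitivity analyses there concerns scale.

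Exposure to the ULEZ is determined by place of schooling (Study design; Study population and setting). The Background says recruitment opened in June 2018 to obtain one year of data before the April 2019 start.

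**The concern.** An interaction depends on the scale of the outcome. Two groups whose FEV1 rises by the same percentage each year, from different levels, have parallel lines on the log scale and diverging lines in ml. Randomisation would make the starting levels equal on average. Here nothing does, and with annual visits and one pre-ULEZ year no child has a pre-ULEZ slope to serve as a check.

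A covariate entered as a main effect shifts the level of the curve, and a random intercept also absorbs only level. Neither changes the slope difference. The direction is not known in advance. A lower London level would hide a true benefit, and a lower Luton level would imitate one. Either would bear directly on the primary research question.

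**Working it through.** **The plan's own figure.** 40 schools × 40 children × 2 sites = 3,200, which matches "The total target sample size is therefore 3,200 children, comprising 1,600 in the London cohort and 1,600 in the Luton cohort". The 90% power cannot be reproduced because no SD of FEV1 growth is given. The standard error needed for that power does not depend on the SD (two-sided 0.05 assumed; the article does not state sidedness):

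SE = 15 / (1.960 + 1.282) = 4.63 ml/year.

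**Inputs not in the article, assumed here.** Mean growth g = 150 to 250 ml/year. Proportional gap p = 2% to 10%.

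**Artefact with no ULEZ effect.** If London FEV1(t) = (1 − p) × Luton FEV1(t) at every t, the slope difference is −p × g. The chance of rejecting a true null is Φ(b/SE − 1.96) + Φ(−b/SE − 1.96), with b = p × g and SE = 4.63.

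| Gap p | g = 150: ml/year (rejection) | g = 200 | g = 250 |
|---|---|---|---|
| 2% | 3.0 (10%) | 4.0 (14%) | 5.0 (19%) |
| 5% | 7.5 (37%) | 10.0 (58%) | 12.5 (77%) |
| 7.5% | 11.2 (68%) | 15.0 (90%) | 18.8 (98%) |
| 10% | 15.0 (90%) | 20.0 (99%) | 25.0 (>99%) |

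The gap that reproduces the whole 15 ml target is 15/g: 10%, 7.5% and 6% for g = 150, 200 and 250.

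**Does covariate adjustment remove it?** Null data were simulated with FEV1 multiplicative in height, age and site, five annual visits, and a random-intercept model with additive covariates. The time × group estimates in ml/year were:

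| Simulation | no gap | 2% | 5% | 7.5% | 10% |
|---|---|---|---|---|---|
| 8,000 per site, growth about 220, attrition and lost visits; age, height, sex | – | −4.7 | −11.4 | −17.0 | −22.6 |
| 1,600 per site, growth about 234, one data set per gap; age, height, ethnicity | +0.5 | – | −11.5 | −20.7 | −22.2 |
| The same, unadjusted | +1.1 | – | −12.4 | −20.6 | −22.0 |

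Adjustment barely changes the result. On log FEV1 with log height, the 1,600-per-site data gave −0.0005 to +0.0001 per year (SE about 0.0004).

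**Gap due only to ethnic mix.** With an assumed 10–13% deficit in one group and a 20–40 point difference in mix, ethnicity as a main effect left −7.0 to −13.6 ml/year. Adding ethnicity × time reduced this to between −2.8 and +2.9.

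**The reverse case.** Suppose London is lower by a constant 85 ml, 5% of an assumed 1,700 ml, and both sites grow 200 ml/year. The ml slopes are then equal. On the log scale the gap goes from ln(1 − 85/1,700) = −0.0513 to ln(1 − 85/2,500) = −0.0346 over four years. That is 0.0167/4 = +0.0042 per year, or about 0.0042 × 2,100 = +9 ml/year at the mid-level. A null simulation of an 85 ml gap, under its own growth model, gave +0.0057 per year (about +12 ml/year, about 10 standard errors). Its ml-scale interaction was about −1 ml/year, the same as with no gap.

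**The case against.** The strongest reply has four parts.

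- **The article does not name the modelling scale.** A target in ml does not force an untransformed model, and a statistical analysis plan not shown may specify logs or covariate-by-time terms. This stands as a limit on certainty. The effect itself is nevertheless fixed in ml per year, and no other scale is mentioned.
- **A simulation that generates proportional gaps will favour the log model.** This stands in full, as the reverse case shows. A reader might infer that log FEV1 should replace ml/year as primary, or that a claim should require significance on both scales. Neither follows. Replacement swaps one untestable assumption for another, and a double requirement costs power. Absolute growth is a legitimate estimand and matches the powered effect.
- **The size of the gap has no support in the article.** This also stands. Study population and setting describes Luton as comparable in air quality, population and deprivation, without giving FEV1 by site. The Background statement that "we identified significant deficits in participating children’s lung capacity of between 5 and 10" per cent might be taken for the expected gap, but it is an association with exposure among east London children and not a between-site FEV1 contrast. The rejection rates are also conditional on the standard error. At the 80% power that the Assumptions section allows for, SE = 15/(1.960 + 0.842) = 5.35, and an 11.4 ml artefact is rejected 57% of the time, against 69% at 4.63.
- **Other analyses are planned.** Effects by ethnic group, deprivation and sex, and the multilevel pollutant models, mean that conclusions will not rest on one coefficient. They partly address ethnic mix but leave the scale question open.

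**Conclusion.** The point holds conditionally. If the sites differ proportionally in FEV1 level at the same age and height, and growth is roughly proportional to level, the primary ml/year interaction is non-zero with no ULEZ effect. It equals about p% of annual growth: 7.5 to 12.5 ml/year for an assumed 5% gap and 150 to 250 ml/year growth, against a 15 ml/year target. Main-effect adjustment and the random intercept do not remove it.

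A reader might go further and infer that the primary result will be biased, or that 3,200 is the wrong sample size. The article supports neither. The size and form of any gap are unknown, a constant gap would leave the ml scale clean, and the power cannot be checked without an SD of growth. What is established is that a non-randomised growth contrast with one pre-ULEZ year and this target is sensitive to scale, and that the article plans nothing that would reveal it.

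**What to change.** Keep the ml/year difference as the primary estimand and pre-specify three additions:

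1. A companion model of log FEV1 with log height and the same other terms, with its time × group interaction converted to ml/year at the cohort mean.
2. Covariate × time terms in the ml model, at least for ethnicity and sex.
3. The baseline FEV1 gap between the sites, adjusted for age and height.

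State the reading rule in advance, including what counts as a material difference in size. If the two scales disagree in direction or materially in size, the growth difference is reported as scale-dependent and is not attributed to the ULEZ.

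The cost is analysis-plan wording and a few extra model runs on data already being collected. The downside is a possibly more cautious conclusion.

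### The primary test compares FEV1 growth, but the only random effect named is an intercept, which does not cover growth differences between children or schools that remain after adjustment

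*Protocol article*

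**What the plan says.** Under Statistical methods, the protocol article analyses post-bronchodilator FEV1 longitudinally: "The model assesses the interaction effect of time and study group to determine the difference in variable change" between London and Luton. The planning target is the same kind of quantity: "We use 90% power and 0.05 significance level to test a 15 ml difference in FEV_1_ growth per year".

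The random-effects structure appears in one sentence: "Mixed effects models using a random intercept term are robust to the biases of missing data and the clustering effect" of recruiting through many schools. It does not say whether the intercept belongs to the child, the school or both. No random slope for time is named at any level. The model adjusts for gender, asthma, ethnicity, deprivation, age, height and BMI.

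The same section describes a three-level model (child, school, group), but for relating pollutants to lung function. It names no random slope and may be reduced to fewer levels. The planned sensitivity analyses change the data analysed (complete histories, outliers, exposure contrasts) and not the random effects. Under Assumptions, the clustering allowance is an "intra-class correlation (ICC) for FEV_1_ in schools calculated from our original ULEZ study (ICC = 0.001", a figure for FEV1 and not for FEV1 growth.

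**The concern.** A random intercept lets children, or schools, start from different FEV1 levels. Given the covariates, it has one time slope per arm. Any remaining spread in individual growth goes into the visit-level residual and is averaged down over visits as if it were measurement noise. But a child's own slope deviation does not average out over that child's visits, and a school's does not average out over its pupils.

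So the statement that a random intercept deals with school clustering does not hold for the contrast being tested. If growth varies, the reported standard error is too small, the confidence interval too narrow, and a chance difference in growth between the two samples is declared a ULEZ effect more often than the stated 5%.

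**Working it through.** **Inputs from the protocol article.** 40 schools per arm and 40 children per school (2 × 40 × 40 = 3,200, as stated); alpha 0.05 (two-sided assumed), power 90%, 15 ml/yr; 70% valid readings; 20% attrition per year; 30% inflation; school ICC 0.001; four annual rounds extended to five, with data collection lost in years 2 and 3 to an extent not given.

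**Inputs not in the document (assumed, shown as ranges).** Residual within-child SD σ; child slope SD τ remaining after covariate adjustment; school slope SD ω. The stated power cannot be reproduced without an SD.

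**Step 1: mechanism, complete data.** With T visits and S the sum of squared centred visit times, per child:
- true variance of the slope = σ²/S + τ²
- variance reported under a random intercept = σ²/S + τ²/(T−1)

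Five visits (S = 10), σ = 100, τ = 40: true 1,000 + 1,600 = 2,600; reported 1,000 + 400 = 1,400. The ratio is 1.86 and its root 1.36. The rejection rate is P(|Z| > 1.96/1.36), about 15%.

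Visits 1, 4 and 5 only (S = 8.67, T = 3), σ = 90, τ = 40: true 935 + 1,600 = 2,535; reported 935 + 800 = 1,735. The ratio is 1.46 and the rejection rate about 10%.

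With τ = 0 the two variances agree and the rate is 5%.

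**Step 2: simulation with the planned losses.** 1,600 per arm, 20% attrition per year, 70% valid readings, σ = 90, no true group difference and no school slope variation. Ranges are across repeated runs (REML random-intercept fits or the within-child estimator).

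| Child slope SD (ml/yr) | Five full rounds | Rounds 2 and 3 both lost |
|---|---|---|
| 0 | about 5% | about 5% |
| 10 | 5–6% | 5–6% |
| 20 | 7–8% | 5–7% |
| 40 | 11–15% | 8–9% |
| 60 | 18–20% | 10–11% |

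With rounds 2 and 3 each half lost, slope SDs of 20, 40 and 60 give about 7%, 11% and 14%. In the five-round REML fits, the empirical SD of the interaction against the mean reported SE was 2.01 against 1.87, 2.87 against 2.11, and 3.71 against 2.46, so the SE is 7%, 26% and 34% too small.

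**Step 3: school slopes.** With k schools per arm and m children per school:
- true variance = 2[ω²/k + (τ² + σ²/S)/(km)]
- reported variance = 2[σ²/S + (τ² + ω²)/(T−1)]/(km)

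Take k = 40, m = 20, five visits, σ = 100, τ = 50. With ω = 0 the rate is 18%. With ω = 10, true = 2[2.5 + 4.375] = 13.75 and reported = 2 × 1,650/800 = 4.125; the ratio is 3.33 and the rate 28%. Adding a child slope but no school slope gives a reported variance of 2 × 3,600/800 = 9.0, a ratio of 1.53 and a rate of about 11%, so both slopes matter if ω > 0. If the ICC of 0.001 also applied to slopes, ω would be 1.6 and the addition trivial (18.2% to 18.5%).

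**Step 4: do the planning figures reveal τ?** 1,600 × 0.7/1.3 × 0.8³ = 441 per arm. With design effect 1.010, solving for 90% power gives an SD of observed growth of 15 × √(441/(1.010 × 2 × 3.2415²)) = 68 ml/yr; with four years of attrition (353 per arm) it is 61. Both include measurement error. With σ = 100 and four visits (S = 5), about √(68.4² − 2,000) = 52 remains as true variation. With σ = 90 and three consecutive visits (S = 2), √(68.4² − 4,050) = 25 remains, and nothing remains from 61. The planning figures do not fix τ.

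**The case against.** The strongest reply is that this is a condensed article and any analysis plan is unseen. The article never says that the intercept is the only random effect; the phrase sits in a general justification and excludes nothing. A reader might infer that the trial has committed to a model without random slopes. The text does not support that, and the absence of a named slope would not be a finding by itself. What remains is the positive claim that a random intercept is robust to school clustering, made in support of a slope comparison. It is wrong as written, whatever another document adds.

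Second, height and BMI are measured every year. Entered as time-varying covariates, they give each child an individual fitted trajectory, so the model does not force equal growth on every child. Only slope variation left after adjustment counts. This stands and may lower the figures, but the document gives nothing from which to say by how much.

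Third, a reader might take a false-positive rate of 15% to 20% as established. It is not: it needs slope SDs of 40 to 60 ml/yr and five full rounds, whereas the article itself reports losses in years 2 and 3. Nor does the back-solved SD of 61 to 68 ml/yr prove real growth variation, as Step 4 shows. The ICC of 0.001 concerns FEV1 level, so it neither supports nor excludes school slope variation.

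**Conclusion.** The point holds in conditional form. The primary contrast is a difference in slopes, the only named random effect covers levels, and the clustering claim does not extend to slopes. Neither the three-level pollutant model, the sensitivity analyses nor the ICC repairs this. The direction is certain wherever growth varies after adjustment; the size is not, because it rests on assumed SDs and on the visit pattern achieved. At σ = 90 and remaining child slope SDs of 20 to 60 ml/yr, the nominal 5% test runs at about 8% to 20% with five full rounds and about 5% to 11% with rounds 2 and 3 both lost. It is close to nominal at a slope SD of 10 or below. School slope variation would come on top. The missing-data half of the same sentence is a separate matter and is not judged here.

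**What to change.** State the primary model with:
- time, group and their interaction as fixed effects, with the listed covariates;
- a random intercept and random time slope for child;
- a random intercept and random time slope for school of enrolment;
- standard errors robust to clustering by school of enrolment as the pre-specified fallback if the school slope does not converge.

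Limit the robustness sentence, as regards clustering, to differences in FEV1 level. Its missing-data part need not be touched for this purpose.

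The cost is analysis wording and possibly wider confidence intervals. No new data are needed, and if growth variation proves negligible little precision is lost. As a check on the remedy, small sets of mixed-model fits (81 to 83 data sets per setting, child slope SD 50, σ = 100) rejected in about 6% with a child slope added, against 19% to 20% with an intercept alone; the Monte Carlo standard error of the 6% is about 2.6 points.

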#### Secondary

Air quality, forced vital capacity (FVC), respiratory symptoms, respiratory infections, physical activity, quality of life, health care use and costs, seroprevalence of SARS-CoV-2 antibodies, and a range of respiratory and health economic data.

Details of outcome measures and the timing and means of their collection are given in Table 1.

**Table 1 Tab1:** Outcome Measures

Type	Outcome	Method	Year 1	Year 2	Year 3	Year 4	Year 5	Recording	Analysis
Primary	FEV_1_	Annual health assessment: spirometry	school visit	school visit	school visit	school visit	school visit	Spirometer download	Interaction analysis
Exposures	Air quality: NO, NO_2_, PM10, PM2.5	k-means clustering developed by Font et al.(27)	LAQN* and AURN**	LAQN and AURN	LAQN and AURN	LAQN and AURN	LAQN and AURN	LAQN and AURN	Interaction analysis
Secondary	FVC and other spirometric variables	Annual health assessment: spirometry	school visit	school visit	school visit	school visit	school visit	Spirometer download	Interaction analysis
Secondary	Physical activity and GPS tracking	Annual health assessment: accelerometer and GPS tracker	school visit	school visit	school visit	school visit	school visit	Accelerometer and GPS download	Interaction analysis
Demography / potential confounding variables		Parent-completed questionnaire: (paper or web)	school bag prior to school visit	school bag prior to school visit	school bag prior to school visit	school bag prior to school visit	school bag prior to school visit	Clinical Record Form	Interaction analysis
Secondary	School absence; work absence	Parent-completed questionnaire: (paper or web)	school bag prior to school visit	school bag prior to school visit	school bag prior to school visit	school bag prior to school visit	school bag prior to school visit	Clinical Record Form	Interaction analysis
Secondary	Respiratory and allergy symptoms (ISAAC^+^)	Parent-completed questionnaire: (paper or web)	school bag prior to school visit	school bag prior to school visit	school bag prior to school visit	school bag prior to school visit	school bag prior to school visit	Clinical Record Form	Interaction analysis
Secondary	QOL (CHU9D^++^)	Parent-completed questionnaire: (paper or web)	school bag prior to school visit	school bag prior to school visit	school bag prior to school visit	school bag prior to school visit	school bag prior to school visit	Clinical Record From	Interaction analysis

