#### Annual study questionnaire for home completion

Caregivers are asked to complete questionnaires in year 1 (when informed consent given to the study) and in study years 2, 3, 4 and 5. These comprise.

Demography and residential history.Parent-reported respiratory and allergy symptoms (ISAAC questionnaire) [32].Parent-reported paediatric quality of life (CHU9D questionnaire) [33].Non-NHS costs.Child absence from school.Smoking/exposure to second-hand smoke during pregnancy.Travel choices.Parental absence from work due to child ill-health.Upon receipt of a completed questionnaire, caregivers receive a £5 supermarket voucher.

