#### Sensitivity analyses and missing data

Sensitivity analyses will be conducted to ensure no bias in the primary results due to missing data by contrasting an “all children” data set to a “complete history” data set. Temporal individual and school exposure assessments will be contrasted to the rest of the cohort to assess for cluster bias such as rebound lung growth and high non-traffic related air pollution change unrelated to the ULEZ.

Z-scores will be calculated for each continuous variable and will be examined for values > 4. Plots of residuals will be inspected for suspected outliers. Should any be found, raw data will be checked for accuracy. If the data are found to be correct, a model will be fitted excluding outliers as a sensitivity analysis to assess impact on the primary data set.

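### Extra covariates may enter the primary FEV1 model after sensitivity results are seen, with no criterion, and one candidate, physical activity, is itself an outcome the ULEZ may change and has an unclear year 5 measurement

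*Protocol article*

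**What the plan says.** Protocol article, Statistical methods. The primary analysis of post-bronchodilator FEV1 is a mixed model with a random intercept: "The model assesses the interaction effect of time and study group to determine the difference in variable change between the intervention group". The core adjustment is definite: "Primary and secondary outcome variables will be adjusted to account for known covariates of gender, asthma diagnosis, ethnicity, deprivation", followed by age, height and BMI, which makes seven covariates. The next sentence leaves room for more: "Secondary covariates which may be included after sensitivity analysis include socioeconomic status, stress, and physical activity".

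Sensitivity analyses and missing data. This section covers three things: missing data ("Sensitivity analyses will be conducted to ensure no bias in the primary results due to missing data by contrasting" all children with those who have a complete history), exposure and cluster bias, and outliers. None of them concerns the choice of covariates.

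Physical activity. Additional assessments limits accelerometry to "study years 1, 2, 3 and 4): Each child is fitted with an Actigraph accelerometer". Table 1 has a row with the method "Annual health assessment: accelerometer and GPS tracker" and shows a school visit in each of years 1 to 5. Physical activity is also listed as a secondary outcome, and a secondary research question asks whether the ULEZ increases it.

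Stress. The word occurs only in the sentence on secondary covariates. The health assessments, the questionnaire list (whose first item is "Demography and residential history"), the additional assessments and Table 1 name no stress measure. The nearest item is coded health-record data "addressing respiratory, mental health, COVID-19 testing and vaccination status, and health care use".

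**The concern.** The study compares two places without randomisation, so covariate adjustment carries much of the inference on the primary question. A rule that lets covariates join the model once sensitivity results are known, without saying what result would bring them in, allows the primary estimate to depend on which version looked better. This is more than a detail left for an analysis plan. The protocol states the rule, and a later plan would have to override it.

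Physical activity adds two problems of its own. First, it may lie on the path from the ULEZ to lung growth. Conditioning on values measured after April 2019 could take out part of the effect that the primary question asks about. Second, if it was not measured in year 5, a model that uses it visit by visit discards the year 5 FEV1 readings. That year was added to replace data lost to COVID-19, and the retained-power statements under Assumptions depend on it.

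**Working it through.** **Design figures.** 40 schools × 40 children × 2 arms = 3,200, which agrees with Sample size. The 90% power for 15 ml/year cannot be reproduced because the article gives no SD of FEV1 growth. The steps below therefore start from 90% power at two-sided 0.05 (the article does not state sidedness) and look only at relative loss. The noncentrality is 1.96 + 1.28 = 3.24.

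**Step 1: how much slope information year 5 carries.** Let Sxx = Σ(t − mean t)², with t in years from the first visit.
- All five visits, t = 0, 1, 2, 3, 4: Sxx = 10. Without year 5: Sxx = 5. Ratio 0.50.
- Years 2 and 3 lost, t = 0, 3, 4: Sxx = 8.67. Without year 5, t = 0, 3: Sxx = 4.5. Ratio 0.52.

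**Step 2: power if year 5 drops out.** The variance of a child's slope is V = g² + r²/Sxx, where g is the between-child SD of growth and r the residual SD. Let R = V(with year 5)/V(without year 5). Power = Φ(3.24 × √R − 1.96). The values of g and r are assumptions.

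| Setting | R | √R | Power |
|---|---|---|---|
| Random intercept only (g = 0), five visits | 0.50 | 0.71 | 63% |
| Random intercept only (g = 0), visits 0, 3, 4 | 0.52 | 0.72 | 65% |
| g = 30, r = 120, five visits: 2,340/3,780 | 0.62 | 0.79 | 72% |
| g = 30, r = 120, visits 0, 3, 4: 2,561/4,100 | 0.62 | 0.79 | 73% |
| g = 40, r = 100, five visits: 2,600/3,600 | 0.72 | 0.85 | 79% |
| g = 40, r = 100, visits 0, 3, 4: 2,754/3,822 | 0.72 | 0.85 | 79% |

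The other two corners (g = 30 with r = 100; g = 40 with r = 120) give 75 to 76%.

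**Step 3: error if the better of two models is reported.** Take one model with year 5 and one without. Under no effect, the two estimates correlate at about √R because one uses a subset of the other's data. For two standard normal statistics with that correlation, the chance that at least one exceeds 1.96 in absolute value is:
- √R = 0.71 to 0.72 (random intercept only): about 8.3%.
- √R = 0.79 to 0.85 (g = 30 to 40, r = 100 to 120): 7.9% down to 7.5%.

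The settings pair up: about 8.3% error goes with 63 to 65% power, and 7.5 to 7.9% with 72 to 79%.

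**Step 4: choice of covariates alone.** Three optional covariates give 2³ = 8 models. In a simplified simulation under no effect (a two-group comparison of means, three independent covariates, assumed correlation with the outcome 0.1 to 0.4), taking the most favourable of the eight gave about 7 to 14% error. This is a worst case and not a model of the planned time-by-group test. It shows only that the inflation does not require any visits to be lost.

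**Step 5: timing.** Recruitment opened in June 2018 to obtain a pre-ULEZ year, and the ULEZ began on 8 April 2019. Year 1 activity values are therefore largely pre-intervention, and later ones are not.

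**The case against.** The strongest reply is that little is really open. Seven covariates are fixed, and of the three extras, socioeconomic status overlaps with deprivation, which is already in the model. The sentence does not say that covariates will be picked by their effect on the time-by-group result, or that an extended model would replace the core one. A core model with extended versions reported beside it is a fair reading, and an analysis plan not shown here may say so. This limits the point to the optional covariates. It does not remove it, because the sentence as written permits the other reading and nothing in the article excludes it.

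Three stronger inferences are tempting, and the document does not support them.
- A reader might conclude that year 5 is lost by design. Table 1 lists a year 5 activity visit, so the two places conflict. Even if the text is right, the loss occurs only if activity is selected, entered per visit and handled without imputation.
- A reader might conclude that stress is not measured. A condensed article may omit an instrument: mental health is named as a secondary outcome in the abstract, also with no instrument given. The article shows only that no measure is named.
- A reader might take the error figures as the trial's error rate. They assume that whichever model is significant is the one reported, which the article does not say will happen.

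**Conclusion.** The point holds in limited form. The core adjustment is settled, but the rule for adding to it has no criterion and operates after results are available, and it reaches the primary model. Among the candidates, physical activity is the clearest problem, as a possible mediator and because its year 5 status is contradictory.

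The size is illustrative because every SD is assumed: roughly 7.5 to 8.3% error instead of 5% if the better of two models is reported. If year 5 drops out, power falls from 90% to 63 to 65% with a random intercept only, the one random term the article names, or to 72 to 79% with the assumed between-child growth variation. The possible removal of part of the effect by adjusting for post-ULEZ activity cannot be sized from the article. The matter should be corrected; it does not invalidate the design.

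**What to change.** - State that the primary FEV1 model adjusts for the seven listed covariates and no others.
- Move socioeconomic status and physical activity to labelled sensitivity analyses, reported beside the primary estimate and never replacing it.
- Use year 1 values in those analyses. Components of the study are opt-in, so year 1 values alone do not keep every child: a child without a valid year 1 record would lose all visits. State a rule for this, for example multiple imputation.
- Reconcile Table 1 with Additional assessments on whether physical activity is measured in year 5.
- Drop stress unless a collected measure is named.

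This costs a few sentences, with no new data and no change to the 3,200 target. The downside is less freedom to refine the primary model later.
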